In addition, we will evaluate a number of secondary topics including: a) baseline differences in CHD prevention practices, b) moderators and mediators of the intervention effect, c) durability of the intervention effect, and d) cost effectiveness of the intervention. For example, some of the secondary hypotheses we will be testing include a) at baseline, CHD prevention practices within the SMMC fell significantly short of attaining guideline-based goals for a range of risk factors; b) at baseline, adherence to prevention guidelines varied directly by SES with adherence being least likely among participants of the lowest SES; c) implementation of the intervention had a greater impact on participants of lower SES thus resulting in a reduction on the magnitude of socioeconomic disparities in CHD prevention; d) changes in patient dietary and exercise habits were the largest mediators of the impact of the intervention; and e) the change in risk factors attributable to intervention was sufficient to achieve reasonable cost-effectiveness relative to other medical therapies.

In the current manuscript, we presented comparisons of baseline characteristics between the two study arms. All statistical analyses were performed in SAS for Windows (SAS Institute, Cary, NC). Frequency distributions, percentages in each group of categorical variables, and means and quartiles for continuous variables were generated for both intervention groups. Student's *t *tests were performed on continuous variables and χ^2 ^tests on categorical variables to assess comparability between the intervention groups at baseline. Statistical significance was set at *p *< 0.05 (two-tailed).

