We will add appropriate covariates into equation (1) to perform the testing of the secondary hypotheses related to moderators and mediators of the intervention effect. For example, these covariates may include SES, change in caloric intake, and change in physical activity. The cost-effectiveness analysis will include: measurement of costs, measurement of changes in quality-adjusted life years (QALYs), and calculation of a cost-effectiveness ratio with an appropriate confidence region. The cost of implementing HTH will be estimated based on the cost of HTH staff time whereas the cost of implementing usual care will be derived from SMMC administrative records. We will estimate a statistical model of QALY changes based on the change in risk of death and, among survivors, the reduction in quality of life due to non-fatal events, which will be approximated using the collected health care utilization data. Using the cost and QALY figures we will estimate an incremental cost-effectiveness ratio, representing the cost per QALY due to the intervention, and a 95% confidence region surrounding the cost-effectiveness ratio using a bootstrapping method. Sensitivity analyses will be performed by varying the underlying model assumptions.

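### Bootstrap limits placed on the cost-per-QALY ratio would mislead if the QALY gain is not clearly above zero; inference on net monetary benefit avoids this at little cost

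*Protocol article*

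**What the plan says.** The analysis is described in the protocol article under *Statistical analysis and hypothesis testing*.

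- **Summary measure:** "we will estimate an incremental cost-effectiveness ratio, representing the cost per QALY due to the intervention".
- **Uncertainty:** "a 95% confidence region surrounding the cost-effectiveness ratio using a bootstrapping method". The same paragraph announces it more loosely as "calculation of a cost-effectiveness ratio with an appropriate confidence region".
- **Inputs:** for QALYs, "We will estimate a statistical model of QALY changes based on the change in risk of death", plus quality-of-life loss from non-fatal events approximated from utilization data. For costs, "The cost of implementing HTH will be estimated based on the cost of HTH staff time", with usual-care costs taken from the medical centre's administrative records.
- **Robustness:** "Sensitivity analyses will be performed by varying the underlying model assumptions".
- **Hypothesis:** secondary hypothesis (e) is that "the change in risk factors attributable to intervention was sufficient to achieve reasonable cost-effectiveness relative to other medical therapies".

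The abstract and the Background name cost-effectiveness beside efficacy as a purpose of the trial. The analysis section lists it among the secondary topics.

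**The concern.** A ratio is a poor scale for uncertainty when its denominator may be zero. As the QALY difference falls through zero, with the cost difference positive, the ratio runs up to plus infinity and reappears at minus infinity. Two replicates that differ trivially in QALYs then sit at opposite ends of the sorted bootstrap distribution, and percentile limits cut that distribution in the wrong places. The sign of the ratio is also ambiguous: +1,500/+0.01 and -1,500/-0.01 both equal 150,000, although the first buys health at a cost and the second saves money by losing health.

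At stake is how the trial reports on one of its stated purposes. Under *Study design*, outcomes data are to guide the handover of the model to the county system, so the cost-effectiveness result may inform a real decision.

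**Working it through.** **1. The plan's own figure.** The article states no figure for cost-effectiveness. Its only related figure is the power of the primary comparison (*Study design*: 400 patients, 5 points, SD 10, α 0.01, 25% loss, 87% power). Lost patients carry baseline or interim values forward. If all of them carry baseline values:
- diluted effect = 5 × (1 − 0.25) = 3.75
- SE = 10 × √(2/200) = 1.0
- two-sided power = Φ(3.75/1.0 − 2.576) = Φ(1.174) = 0.880, or 0.877 with the noncentral t

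This agrees with the stated 87%. The planned effect on risk is thus 3.75 SE, and half of it is about 1.9 SE. These serve as reference points for the QALY gain, **on the assumption** that its precision tracks that of the risk score.

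**2. When do percentile limits on the ratio change sign?** Assume normal sampling distributions and a true cost difference of 5 SE, so that almost every cost replicate is positive. A replicate ratio is then negative exactly when its QALY difference is negative. The 2.5% and 97.5% limits have opposite signs when more than 2.5% of replicates lie on each side of zero QALYs, that is, when the observed QALY z lies between −1.96 and 1.96. This is also the condition for an unbounded Fieller set. With true QALY gain z (in SE):

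P(limits span both signs) = Φ(1.96 − z) − Φ(−1.96 − z)

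| True QALY gain (SE) | Formula | Simulation (4,000 trials × 2,000 replicates) |
|---|---|---|
| 3.75 | 3.7% | 3.4% |
| 2.5 | 29.5% | 29% |
| 1.9 | 52.4% | 52% |
| 1.0 | 83.0% | 83% |
| 0 | 95.0% | 95% |

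Repeat simulations gave 3 to 5%, 29 to 30%, 52 to 54%, 82 to 84% and 95%.

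**3. What such an interval looks like.** Illustrative inputs, none from the article: observed cost difference 1,500 (SE 300), SE of the QALY difference 0.01.

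| Observed QALY z | Replicates with QALY difference ≤ 0 | 95% percentile limits on the ratio |
|---|---|---|
| 0.5 | 31% | −2.1 to +2.2 million |
| 1.0 | 16% | −1.3 to +1.5 million |
| 1.5 | 6% | −0.64 to +0.91 million |
| 3.75 | about 0% | 21,000 to 89,000 |

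Take z = 1. The interval contains 10,000 per QALY, which these data reject: 10,000 × 0.01 − 1,500 = −1,400, with SE √(100² + 300²) = 316, so z = −4.4. It shuts out arbitrarily large ratios, yet those correspond to no QALY gain, which the data do not reject (z = 1). So the limits admit a value that the data rule out and exclude values that the data allow.

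**4. The same case as net monetary benefit (NMB).** NMB = λ × QALY difference − cost difference, and SE = √((λ × 0.01)² + 300²) if the two differences are independent. At z = 1:

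| λ per QALY | NMB | SE | 95% CI | P(NMB > 0) |
|---|---|---|---|---|
| 50,000 | −1,000 | 583 | −2,143 to 143 | about 0.04 |
| 100,000 | −500 | 1,044 | −2,546 to 1,546 | 0.32 |
| 200,000 | 500 | 2,022 | −3,464 to 4,464 | 0.60 |

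These results are ordered and readable. In simulation, NMB intervals at 50,000 covered the true value in 94 to 96% of trials for true QALY gains from 0 to 5 SE.

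**The case against.** **The text says region, not interval.** A bootstrap region can be a joint region on the cost-QALY plane, which stays readable across zero QALYs, and the article also promises an appropriate one. This stands as an ambiguity. Placing the region around the ratio suggests limits on the ratio, but one clarifying sentence would settle that part.

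**Thresholds and acceptability curves are detail for a fuller document.** This also stands: the lack of a cost-per-QALY threshold in a journal article is not a fault in itself. The point here concerns the ratio-based summary that the article does state.

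**The size comes from assumptions.** True. The article gives no expected cost or QALY difference and no variance, and nothing in it shows that the QALY gain will be small. At the one scenario tied to the design, 3.75 SE, the problem is rare. With a cost difference of 5 SE, moreover, a negative ratio nearly always means costlier and less effective, so the ambiguity of sign hardly arises in these simulations. The ordering problem is what remains.

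**Net benefit does not make weak data strong.** Correct: at z = 1, all three NMB intervals above include zero.

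**A stronger reading is tempting but unsupported.** A reader might infer that the planned analysis can give no interpretable answer, or that no result could confirm or refute hypothesis (e). The article does not support this. A clearly dominant programme, or a tight interval of positive ratios such as 21,000 to 89,000, could be set against other therapies, which the hypothesis names as its comparator.

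**Conclusion.** The point holds as a conditional weakness. If the planned region is a pair of limits on the ratio, it misleads when the QALY gain is not clearly above zero. Under the assumptions above (normal estimates, cost difference 5 SE), limits of opposite sign would occur in about 3% of trials at a QALY gain of 3.75 SE, about 29% at 2.5 SE, about 53% at 1.9 SE and about 82% at 1 SE. Which scenario applies cannot be told from the article. The primary test, the sample size and data collection are unaffected. A better standard summary is available from the same replicates, so the change is worth making, as an inexpensive improvement to a secondary analysis.

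**What to change.** 1. Keep the bootstrap, resampling each patient's cost and QALY values together, and report the ratio as a point estimate.
2. State that the 95% region is the joint distribution of cost and QALY differences, and plot the replicates on the cost-effectiveness plane.
3. Base inference on net monetary benefit with its 95% CI, and on an acceptability curve, over a range of cost-per-QALY thresholds stated in advance.
4. Judge hypothesis (e) on that scale.

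The cost is about a paragraph of analysis text, agreement on the threshold range, and a little extra output from the same bootstrap samples. No new data are needed. Weak data may still leave (e) undecided, but the report would show this plainly.

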## Results

We achieved equal distributions of the demographic, biophysical and lifestyle characteristics between the two intervention groups. Each of these categories is reviewed below, with an emphasis on the aggregate characteristic of the entire population.

### Demographic characteristics (Table 2)

**Table 2 T2:** Demographic characteristics of HTH participants relative to San Mateo County and the U.S. population^1^

		**HTH**^2^	**San Mateo County**	**U.S.**
**Mean Age in years (SE)**		55.7 (0.5)	53.7 (0.5)	54.3 (0.2)
**Sex **(%)	Male	34.6	47.8	47.4
	Female	65.4	52.2	52.6
**Ethnicity **(%)	Hispanic or Latino	62.8	14.9	10.2
	Non-Hispanic White	15.5	59.0	73.7
	African American	9.5	0.8	10.5
	Asian/Pacific Islander	12.2	22.9	4.2
	Other	0	2.4	1.4
**Education **(%)	< High School	61.3	16.1	15.2
	High School Graduate	15.9	15.3	32.3
	Some College	13.3	25.5	25.1
	College Graduate	8.9	43.1	27.3
**Marital Status **(%)	Never Married	16.5	14.6	9.9
	Married/Living with a Partner	39.3	62.0	64.1
	Separated	18.8	7.1	4.2
	Divorced	12.4	7.1	13.0
	Widowed	9.6	9.2	8.8
**Employment Status **(%)	Employed	38.2	63.5	61.3
	Unemployed	26.2	3.6	2.2
	Disabled or Otherwise Not in Labor Force	18.8	7.7	22.7
	Retired	13.9	25.1	13.8

^1^Estimates for San Mateo County and U.S. populations are based on the January 2006 Current Population Survey of adults between the ages of 35 and 85.

^2^The percentages for education, marital status and employment status do not add up to 100% because of missing data.

The mean age of HTH participants at baseline was 56 years (range 31 to 85 years). One participant whose age was 31 years at enrollment was randomized because of an incorrect date of birth, which was later rectified. We had expected to recruit an ethnically diverse population, including Latinos/Hispanics (55%) and other minorities (25%). The final sample consisted of 63% Latinos/Hispanics, 12% Asians and Pacific islanders, and 10% African Americans. In addition, 65% of the participants were female, 61% had less than a high school education, and 62% were not employed at the time due to unemployment, disability or retirement. This demographic profile differs from that of San Mateo County and of the U.S. as being more ethnically diverse and socioeconomically disadvantaged.

We also examined the distribution of participants by gender and ethnicity (Latinos/Hispanics vs. others) across the four study sites. The distribution of gender was comparable among clinics with women accounting for 59% of the participants in the South San Francisco clinic (total n = 100), 62% in the Menlo Park clinic (109), and 70% in the Redwood City (127) and Daly City clinics (83). The distribution of ethnicity varied across clinics. Eighty-seven percent of participants from the Redwood City clinic were Hispanic, accounting for 42% of all Hispanics in the entire sample. In addition, 78% of all blacks in the sample were from the Menlo Park clinic.

### Baseline medical therapies (Figure 3)

**Figure 3 F3:**
[figure not shown]
Proportion of randomized participants with specific diagnoses who were prescribed appropriate medication at baseline.

Prior to randomization, a large proportion of participants were taking medications for specific medical conditions. Eighty-nine percent of participants who had been diagnosed with hypertension received prescriptions for antihypertensive medications, and 69% of those with hyperlipidemia were prescribed lipid-lowering medications. Insulin or oral hypoglycemic agents were prescribed among 88% of participants with diabetes mellitus. Also, 64% of those with CVD or diabetes were taking aspirin. The proportion being treated at baseline for the selected conditions did not differ by sex and ethnicity.

The cardiovascular health profile of the HTH cohort strongly suggests a need for intensive cardiovascular risk reduction interventions, particularly lifestyle risk factor interventions. The interrelatedness of cardiovascular risk factors demands an integrated approach to management. However, the current US health care system lacks the capability of providing effective and cost-conscious CVD risk reduction interventions, particularly for ethnic minorities and low-SES populations [4-6]. Chronic disease management exerts tremendous time demands on PCPs [3,36] such that achieving guideline-accordant practice is unlikely unless physicians work as part of a health care team in which there is efficient division of labor. Case management provides an excellent team-approach model for integrating multiple risk reduction into practice that strives to meet nationally established goals for CVD risk reduction. Compared to usual care, case management has been shown to improve the delivery of care as well as resulting cardiovascular outcomes among predominantly white, high-risk patients [7-10]. Data are only beginning to accumulate with regard to the effectiveness of case management among ethnic minorities [11].

The HTH case management program is based on a model that has evolved through several previous clinical trials [7,8]. The model provides a systematic approach to the comprehensive, individualized and intensive management of cardiovascular risk in at-risk patients. It is based on the premise that cardiovascular risk reduction is synergistic and that CVD prevention and management is most successful when lifestyle interventions are integrated with appropriate medical therapies. At the core of the model is a team of nurses and dietitians (case managers) capable of treating hypertension, dyslipidemia, diabetes, obesity, physical inactivity, and smoking cessation. Case managers provide long-term counseling based on clinical status, risk level, interest in and readiness for change, and personal resources. Case managers' activities are integrated with the activities of the patient's PCP. Case management goals are modeled on latest practice guidelines.

To conclude, baseline characteristics of HTH participants suggest that we have recruited an appropriate cohort in which to implement a case management approach and test its efficacy and cost-effectiveness. Due to its unique composition of ethnic minorities and persons of low-SES, the HTH will enrich the U.S. literature regarding better strategies for CVD prevention among these priority population groups and aid in guiding future practice that will reduce health disparities. The HTH experience also will be of considerable learning value for health care systems in Canada, the United Kingdom, and other countries that have shown increasing interest in the clinical utility of the case management model [37-39]. Our experience to date has led to success in a number of areas that are likely to translate into final success of the project. Among these: 1) developing a mutually supportive and productive collaboration with SMMC; 2) developing the HTH model both in terms of its intellectual and evidence-based foundation, as well as all its logistical elements; 3) successfully recruiting slightly more than the expected number of patients; 4) recruiting and retaining a cohesive staff of providers and researchers; 5) eliciting a favorable response from San Mateo County regarding the intervention and plans to disseminate the intervention to additional clinical sites as a County-run program.
